## **9 STUDY PROCEDURES AND FLOW CHART**

**9.1 Study Flow Chart**

| Activity                                | Visit 0
Screening | Visit 1
Baseline | Visits 2-6                                          | Visit 7
Month 3 | Visits 8-13                     | Visit 14
Month 6 | Visits 15-19                | Visit 20
Month 9 | Visits 21-27                    | Visit 28 |
|-----------------------------------------|----------------------|---------------------|-----------------------------------------------------|--------------------|---------------------------------|---------------------|-----------------------------|---------------------|---------------------------------|----------|
|                                         | Day
-25±10        | Day 1               | Weeks 2,
4  , 6, 8  , 10 | Week 12            | Weeks 14, 16,
18, 20, 22, 24 | Week 26             | Weeks 28,
30, 32, 34, 36 | Week 38             | Weeks 40, 42,
44, 46, 48, 50 | Week 52  |
| Sign informed consent                   | X                    |                     |                                                     |                    |                                 |                     |                             |                     |                                 |          |
| Demographics                            | X                    |                     |                                                     |                    |                                 |                     |                             |                     |                                 |          |
| Medical history                         | X                    |                     |                                                     |                    |                                 |                     |                             |                     |                                 |          |
| Current/Concomitant medications         | X                    | X                   | X                                                   | X                  | X                               | X                   | X                           | X                   | X                               | X        |
| Weight/height                           | X                    | X                   |                                                     | X                  |                                 | X                   |                             | X                   |                                 | X        |
| Physical examination                    | X                    | X                   |                                                     | X                  |                                 | X                   |                             | X                   |                                 | X        |
| Glucocerebrosidase activity             | X                    |                     |                                                     |                    |                                 |                     |                             |                     |                                 |          |
| Platelet count / hemoglobin (local lab) | X        | X                   | X                                                   | X                  |                                 | X                   |                             | X                   |                                 | X        |
| Haematology                             | X                    | X                   | X                                                   | X                  |                                 | X                   |                             | X                   |                                 | X        |
| Biochemistry                            | X                    | X                   | X                                                   | X                  |                                 | X                   |                             | X                   |                                 | X        |
| Serology (HIV, HBsAg, HCV)              | X                    |                     |                                                     |                    |                                 |                     |                             |                     |                                 |          |
| TSH, transferrin, B12 and folic acid    | X                    |                     |                                                     |                    |                                 |                     |                             |                     |                                 |          |
| Beta HCG (post-menarchal girls)         | X                    |                     |                                                     |                    |                                 |                     |                             |                     |                                 |          |
| Urinalysis                              | X                    | X                   | X                                                   | X                  |                                 | X                   |                             | X                   |                                 | X        |
| Review inclusion/exclusion criteria     | X                    |                     |                                                     |                    |                                 |                     |                             |                     |                                 |          |
| Anti-taliglucerase alfa antibodies      |                      | X                   |                                                     | X                  |                                 | X                   |                             | X                   |                                 | X        |
| Organ volumes (MRI/ultrasound)          |                      | X                   |                                                     |                    |                                 |                     |                             |                     |                                 | X        |
| Tanner Stage                            |                      | X                   |                                                     |                    |                                 | X                   |                             |                     |                                 | X        |
| Echocardiography                        |                      | X                   |                                                     |                    |                                 |                     |                             |                     |                                 | X        |
| Left Hand and wrist X-ray evaluation    |                      | X                   |                                                     |                    |                                 |                     |                             |                     |                                 | X        |
| Quality of Life (CHQ PF-28)             |                      | X                   |                                                     |                    |                                 | X                   |                             |                     |                                 | X        |
| Chitotriosidase or CCL18 biomarker      |                      | X                   |                                                     | X                  |                                 | X                   |                             | X                   |                                 | X        |
| Mutation analysis                       |                      | X                   |                                                     |                    |                                 |                     |                             |                     |                                 |          |
| DEXA                                    |                      | X                   |                                                     |                    |                                 |                     |                             |                     |                                 | X        |
| IV Infusion (ERT)                       |                      | X                   | X                                                   | X                  | X                               | X                   | X                           | X                   | X                               | X        |
| Adverse Events                          |                      | X                   | X                                                   | X                  | X                               | X                   | X                           | X                   | X                               | X        |

Haemoglobin and platelets (local laboratory), haematology, biochemistry and urinalysis will be performed at Screening, Baseline, Weeks 4, 8 and 12 and then every 3 months.

Include blood smear

---

## **9.2 Study Visits**

### **9.2.1 Screening (Visit 0, Day -25 ± 10)**

1. Obtain written informed consent from the subject and/or parent or gaurdian
2. Assign screening number
3. Demographics
4. Medical history
5. Physical examination, including weight and height
6. Current medications
7. Clinical laboratory tests
  - Blood platelet count including blood smear and hemoglobin (local)
  - Haematology
  - Biochemistry
  - Urinalysis
  - Thyroid stimulating hormone (TSH)
  - Transferrin
  - Vitamin B12
  - Folic Acid
  - Glucocerebrosidase activity
  - Blood pregnancy test (beta-HCG) for female subject of child-bearing potential
  - Serology for HIV, HBsAg, HCV
8. Review all inclusion and exclusion criteria and determine subject's eligibility
9. Request for subject approval and randomization

### **9.2.2 Visit 1 (Baseline, Day 1)**

1. Assign to randomized treatment group
2. Concomitant medications
3. Physical examination including weight and height
4. MRI or ultrasound for spleen and liver volume
5. Echocardiography (for tricuspid insufficiency gradient)
6. Clinical laboratory tests
  - Blood platelet count and hemoglobin (local)
  - Haematology
  - Biochemistry
  - Urinalysis
  - Anti-taliglucerase alfa antibody
  - Biomarkers: chitotriosidase or CCL18
  - Mutation analysis
7. Left hand and wrist X ray for bone age
8. Tanner Stage
9. DEXA
10. Quality of Life (CHQ PF-28)
11. Taliglucerase alfa infusion

---

## 12. Adverse events

Perform the following procedures for the taliglucerase alfa dosing:

- Observe the subject clinically during and for a minimum of 1 hour after dosing.
- Evaluate vital signs every 15 minutes for the first hour and then every 30 minutes if the subject tolerates the infusion
- Evaluate the injection site
- A follow up telephone call with the subject will be held the day after the infusion

The subject should be reminded of the date of their next visit.

### 9.2.3 Visits 2 – 6 (Weeks 2, 4, 6, 8, 10 $\pm$ 3 Days)

Subjects will receive their taliglucerase alfa infusion at the selected medical center. Perform the following procedures for the taliglucerase alfa dosing:

- Observe the subject clinically for a minimum of 1 hour after dosing.
- Evaluate vital signs every 30 minutes if the subject has tolerated well previous infusions. Otherwise, evaluate vital signs every 15 minutes for the first hour.
- Evaluate the injection site.

Record adverse events and concomitant medications at each visit.

Laboratory tests [haemoglobin and platelets (local laboratory), haematology, biochemistry, urinalysis and anti-taliglucerase alfa antibody test] will be performed at visits 3 and 5.

Remind the subject of the date of their next visit.

### 9.2.4 Visit 7 (Month 3, Week 12 $\pm$ 7 Days)

Perform the following assessments:

1. Adverse events and concomitant medications
2. Physical examination including weight and height
3. Clinical laboratory tests
  - Blood platelet count and hemoglobin (local lab)
  - Haematology
  - Biochemistry
  - Biomarkers: chitotriosidase or CCL18
  - Anti-taliglucerase alfa antibody test
  - Urinalysis
4. Taliglucerase alfa infusion

Perform the following procedures for taliglucerase alfa dosing:

- 
- Observe the subject clinically for 1 hour after dosing.
  - Evaluate vital signs every 30 minutes
  - Evaluate the injection site.

Subjects who tolerate the infusions well are eligible after this visit for transfer to home or infusion center treatment at the discretion of the investigator and Medical Director. The procedures to be followed will depend on local standards of care and procedures established at the center for administration of home care.

Remind the subject of the date of their next visit.

#### **9.2.5 Visits 8 – 13 (Weeks 14, 16, 18, 20, 22, 24 ± 3 days)**

Subjects will receive their taliglucerase alfa infusion at the selected medical center. Perform the following procedures for taliglucerase alfa dosing:

- Observe the subject clinically for 1 hour after dosing.
- Evaluate vital signs every 30 minutes
- Evaluate the injection site.

Record adverse events and concomitant medications at each visit.

Remind the subject of the date of their next visit.

#### **9.2.6 Visit 14 (Month 6, Week 26 ± 7 days)**

1. Adverse events and concomitant medications
2. Physical examination including body weight and height
3. Clinical laboratory tests
  - Blood platelet count and hemoglobin (local lab)
  - Haematology
  - Biochemistry
  - Biomarkers: chitotriosidase or CCL18
  - Anti human taliglucerase alfa antibody test
  - Urinalysis
4. Tanner Stage
5. Quality of Life
6. Taliglucerase alfa infusion

Perform the following procedures for taliglucerase alfa dosing:

- Observe the subjects clinically for 1 hour after dosing.
- Evaluate vital signs every 30 minutes
- Evaluate the injection site.

Remind the subject of the date of their next visit.

**9.2.7 Visit 15 – 19 (Weeks 28, 30, 32, 34, 36  $\pm$  3 days)**

Subjects will receive their taliglucerase alfa infusion at the selected medical center. Perform the following procedures for taliglucerase alfa dosing:

- Observe the subjects clinically for 1 hour after dosing.
- Evaluate vital signs every 30 minutes
- Evaluate the injection site.

Record adverse events and concomitant medications at each visit.

Remind the subject of the date of their next visit.

**9.2.8 Visit 20 (Month 9, Week 38  $\pm$  7 days)**

Perform the following assessments:

1. Adverse events and concomitant medications
2. Physical examination including weight and height.
3. Clinical laboratory tests
  - Blood platelet count and hemoglobin (local lab)
  - Haematology
  - Biochemistry
  - Urinalysis
  - Anti-taliglucerase alfa antibodies
  - Biomarkers: Chitotriosidase or CCL18
4. Taliglucerase alfa infusion

Perform the following procedures for taliglucerase alfa dosing:

- Observe the subject clinically for a minimum of 1 hour after dosing
- Evaluate vital signs every 30 minutes
- Evaluate the injection site.

Remind the subject of the date of their next visit.

**9.2.9 Visit 21 – 27 (Weeks 40, 42, 44, 46, 48, 50  $\pm$  3 days)**

Subjects will receive their taliglucerase alfa infusion at the selected medical center. Perform the following procedures for taliglucerase alfa dosing:

- 
- Observe the subject clinically for 1 hour after dosing.
  - Evaluate vital signs every 30 minutes
  - Evaluate the injection site.

Record adverse events and concomitant medications at each visit.

Remind the subject of the date of their next visit.

#### **9.2.10 Visit 28 (Month 12, Week 52 $\pm$ 7 days)**

Perform the following assessments:

1. Adverse events and concomitant medications
2. Physical examination including weight and height.
3. Clinical laboratory tests
  - Blood platelet count and hemoglobin (local lab)
  - Haematology
  - Biochemistry
  - Urinalysis
  - Anti-taliglucerase alfa antibodies
  - Biomarkers: Chitotriosidase or CCL18
4. Quality of life
5. Echocardiography
6. Spleen and liver volume by MRI or ultrasound
7. Tanner Staging
8. Left hand and wrist X-ray for bone age
9. DEXA
10. Taliglucerase alfa infusion

Perform the following procedures for taliglucerase alfa dosing:

- Observe the subject clinically for a minimum of 1 hour after dosing
- Evaluate vital signs every 30 minutes
- Evaluate the injection site.

Protocol Number PB-06-005

Protalix Ltd.  
April 28, 2010

---

## **10 STATISTICAL METHODS PLANNED AND SAMPLE SIZE**

Protocol Number PB-06-005

Protalix Ltd.  
April 28, 2010

---

---

## **11 QUALITY CONTROL AND QUALITY ASSURANCE**

### **11.1 Source Data and Records**

Source data are all the information in original records and certified copies of original records of clinical findings, observations, laboratory reports, data sheets provided by the sponsor or other activities in the study, which are necessary for the reconstruction and evaluation of the study. The investigator will permit study-related monitoring, audit(s), IRB review(s) and regulatory inspection(s), with direct access to all the required source records.

All study records will be retained for a period of time as defined by the regulatory authority for the country in which the investigation is conducted. Generally, this means at least 2 years following the date on which the drug is approved by the regulatory authority for marketing for the purposes that were the subject of the investigation. In other situations (e.g., where the investigation is not in support of or as part of an application for a research or marketing permit), a period of 2 years following the date on which the entire clinical program is completed, terminated or discontinued or the investigational application under which the investigation is being conducted is terminated or withdrawn by the regulatory authorities.

In the event the Investigator retires, relocates or for any other reason withdraws from the responsibility for maintaining records for the period of time required, custody of the records may be transferred to any other person who will accept responsibility for the records. Notice of such a transfer must be given in writing to the Sponsor. The Investigator must contact the Sponsor prior to disposal of any records related to this study.

### **11.2 Reporting of Results**

The Case Report Form (CRF) is an integral part of the study and subsequent reports. The CRF must be used to capture all study data recorded in the subject's medical record. The CRF must be kept current to reflect subject status during the course of the study. Only a subject screening and randomization number and subject initials will be used to identify the subject.

The monitor is responsible for performing on-site monitoring at regular intervals throughout the study to verify adherence to the protocol; verify adherence to local regulations on the conduct of clinical research; and ensure completeness, accuracy, and consistency of the data entered in the CRF.

Protalix Ltd. or their designee will monitor completed Case Report Forms (CRFs). A case report form will be provided for each screened subject.

All protocol-required information collected during the study must be entered by the Investigator, or designated representative, in the Target e\*CRF™, an Internet-based electronic data collection system. All details of the CRF completion and correction will be explained to the investigator. The management module of Target e\*CRF™ includes edit check and query systems that seamlessly integrate with the data entry system. All modifications to the data in the eCRF are tracked by an electronic audit trail (date and identity of the person making the change are instantaneously recorded). Target e\*CRF™ is 21CFR Part 11 compliant.

---

If the Investigator authorizes other persons to make entries in the CRF, the names, positions, and signatures of these persons must be supplied to the sponsor.

The Investigator, or designated representative, should complete the eCRF as soon as possible after information is collected, preferably on the same day that a study subject is seen for an examination, treatment, or any other study procedure. Any outstanding entries must be completed immediately after the final examination. By design, an explanation must be provided for all missing data, altered data, and/or out of range data.

The completed case report form must be reviewed and signed by the Investigator named in the study protocol or by a designated sub investigator.

Final monitored and audited eCRFs will be provided by the Sponsor to the sites at the end of the study in the format of a PDF file.

### **11.3 Confidentiality of Subject Data**

The investigator will ensure that the confidentiality of the subjects' data will be preserved. In the CRF or any other documents submitted to the sponsor, the subjects will not be identified by their names, but by an identification system, which consists of their initials and number in the study. The investigator will maintain documents not meant for submission to the sponsor, e.g., the confidential subject identification code and the signed informed consent forms, in strict confidence.

---

## **12 REPORTING AND PUBLICATION**

### **12.1 Confidentiality of Study Data**

Any information relating to the study product or the study, including any data and results from the study, will be the exclusive property of the sponsor. The investigator and any other persons involved in the study will protect the confidentiality of this proprietary information belonging to Protalix Ltd..

### **12.2 Publication Policy**

Protalix Ltd. agrees to make the report of the multicenter study results available to investigators for preparing a publication of the results in meeting abstract or medical journal form. Protalix Ltd. will have 30 days to review any proposed publication of the data for accuracy and proprietary information.

### 13.1 Appendix 1. Vial Label

[figure not shown]

---

**13.2 Appendix 2. Infusion Rate Algorithm**

The infusion rate (IR) may be adjusted according to individual subject symptoms and signs. The assumptions with respect to adverse experiences to the infusion are:

1. Most of the subjects will tolerate the infusion without any special symptom or event. The infusion rate may be increased over time to the maximal rate 2.25 ml/minor after discussion with the Medical Monitor (an infusion duration of 1 hour).
2. Subjects presenting symptoms and signs of **severe** hypersensitivity will be evaluated according to the WHO Drug Toxicity criteria and there may be a discontinuation of treatment according to the protocol.
3. Subjects may present signs and symptoms that will respond to reducing of the infusion rate and may not appear at the next infusion.
4. Tolerability and the subject specific infusion rate will be assessed and decided by the Investigator according to vital signs and clinical status of the subject.

Definitions to be applied regarding tolerability of infusions are as follows:

| Good tolerability                                                                                                       | Partial tolerability                                                                                                           | Poor tolerability                                                                                                                                                            |
|--------------------------------------------------------------------------------------------------------------------------------|---------------------------------------------------------------------------------------------------------------------------------------|-------------------------------------------------------------------------------------------------------------------------------------------------------------------------------------|
| Infusion was performed without Signs and symptoms (such as burning, pruritus, flushing, discomfort, or change in vital signs). | Signs and symptoms appeared during the infusion and resolved after slowing infusion rate or at the end of the infusion. | Signs and symptoms meeting the definitions of WHO Grade 1 or 2 toxicity responding to reduction of infusion rate or responding to treatment (example, antihistamine for urticaria). |

The specific algorithm to be followed is below.

[figure not shown]

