#### **6.3.3 Removal of Subjects from Therapy or Assessment**

Reasons for permanent discontinuation include the following:

- The subject experiences two or more Grade 3 toxicities or one or more Grade 4 toxicity considered by the investigator associated with taliglucerase alfa treatment (see Sections 8.2.4 Adverse Events and 13.5, Appendix 5 WHO Common Toxicity Criteria)

- Subjects who experience progressive hypersensitivity or severe hypersensitivity will be treated appropriately and withdrawn from the study (see Appendix 2 and Appendix 3)
- The subject requests to discontinue treatment
- Investigator feels that it is not in the best interest of the subject to continue treatment and/or if the investigator believes the subject can no longer be compliant with the requirements of the study.

For any discontinuation, the Investigator will obtain all the required details and document the date and the main reason for the premature termination. If the reason for discontinuation is an adverse event, the specific event or the main laboratory abnormality will be recorded in the CRF. The Investigator will make thorough efforts to document the outcome. The Investigator will attempt to continue to follow the subject for the full duration of the study or at least for 30 days following discontinuation. If circumstances prevent the subject from completing all visits, every attempt will be made to complete all procedures listed in Section 9 for Visit 28.

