##### Progressive

- Erythematous or massive urticarial rash
- Edema of face, neck, soft tissues

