##### Severe

- Hypotension
- Bronchospasm (wheezing)
- Laryngeal edema (dyspnea, stridor, aphonia, drooling)
- Arrhythmias

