#### **Treatment algorithm**

With the onset of any of the above clinical signs, immediately discontinue study medication administration and initiate the following monitoring.

- Continuous electrocardiographic monitoring
- Continuous pulse oximetry
- Measure blood pressure every 5 minutes
- Perform chest auscultation every 5 minutes

- 
- Blood samples need to be collected for Tryptase (29-33) and antibodies. Tryptase samples need to be withdrawn at:
    - 1st sample taken 0.25-3 hours after onset of symptoms
    - 2nd sample taken between 3-6 hours
    - 3rd sample taken 24-48 hours to verify the return to baseline.

In the case of progressive or severe hypersensitivity, treat appropriately and withdraw the subject from the study.

Treat as follows:

Urticaria or edema of the face, neck, or soft tissues

- Epinephrine 1:1000 solution, 0.5 mL subcutaneously, repeat as needed every 5-10 minutes
- Antihistamines
- Corticosteroids

Hypotension (systolic blood pressure (SBP)  $\leq$  90 mmHg)

- Isotonic sodium chloride solution, 1 L every 30 minutes as needed to maintain SBP > 90 mmHg
- Epinephrine 1:10,000 solution given IV at 1 µg/minute initially, then 2-10 µg/minute to maintain SBP > 90 mmHg
- Norepinephrine 4 mg in 1 L 5% dextrose in water given IV at 2-12 µg/min to maintain SBP > 90 mmHg
- Glucagon 1 mg in 1 L 5% dextrose in water give IV at 5-15 µg/minute for refractory hypotension

Bronchospasm

- Oxygen by face mask at 6-8 L/minute to maintain oxygen saturation at > 90%
- Epinephrine 1:1000 solution, 0.5 mL subcutaneously
- Albuterol 0.5 mL of 0.5% solution in 2.5 mL of sterile saline every 15 minutes up to three doses
- Inhaled beta-agonists
- Corticosteroids

Laryngeal edema

- Epinephrine 1:1000 solution, 0.5 mL subcutaneously, repeat as needed every 5 to 10 minutes
- Corticosteroids

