**Premedication**

Premedication for subsequent taliglucerase alfa infusions may be considered at the discretion of the investigator and Medical Director for subjects experiencing early clinical signs of hypersensitivity or rash/urticaria that responds promptly to oral antihistamine administration (see also Appendix 2 for adjustment of infusion rate). The premedication will be applied according to the following steps as needed to prevent progressive hypersensitivity:

1. Antihistamine (H1 blocker: diphenhydramine, hydroxyzine, cetirizine, loratadine, desloratidine) at a standard dose 12 hours and 2 hours before the start of the infusion.
2. H1 blocker plus H2 blocker (ranitidine, cimetidine, famotidine) at standard doses 12 hours and 2 hours before the start of the infusion.
3. H1 blocker plus H2 blocker plus prednisone up to 50 mg administered 12 hours and 2 hours before the start of the infusion.

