| Category                | Toxicity                | Grade0                                     | Grade1                                      | Grade2                                                  | Grade3                                                       | Grade4                                                               |
|-------------------------|-------------------------|--------------------------------------------|---------------------------------------------|---------------------------------------------------------|--------------------------------------------------------------|----------------------------------------------------------------------|
| Allergy                 | Allergy                 | none                                       | transient rash, drug fever < 38°C (100.4°F) | urticaria, drug fever 38°C (100.4°F), mild bronchospasm | serum sickness, bronchospasm requiring parenteral medication | anaphylaxis                                                          |
| Local                   | Local                   | none                                       | pain                                        | pain and swelling with inflammation or phlebitis        | ulceration                                                   | plastic surgery indicated                                            |
| Fever of unknown origin | Fever of unknown origin | none                                       | 37.1 - 38.0° C 98.7° - 100.4° F             | 38.1 - 40.0°C 100.5 - 104°F                             | > 40.0°C > 104.0°F for less than 24hrs                       | > 40.0°C (>104°F) for more than 24 hrs or accompanied by hypotension |
| Infection               | Infection               | none                                       | mild                                        | moderate                                                | severe                                                       | life-threatening                                                     |
| Additional events       | Asthenia                | Analogous to Karnofsky index (WHO grading) |                                             |                                                         |                                                              |                                                                      |

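### Severe hypersensitivity means withdrawal in the synopsis, Section 6.3.3 and Appendix 3 but only possible discontinuation after WHO grading in Appendix 2, and the two scales class bronchospasm differently

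*Protocol*

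**What the plan says.** Four places in the protocol set out what follows severe hypersensitivity.

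- **Section 6.3.3:** "Subjects who experience progressive hypersensitivity or severe hypersensitivity will be treated appropriately and withdrawn from the study". The same bullet refers the reader to both Appendix 2 and Appendix 3. The synopsis carries the same rule.
- **Appendix 3, treatment algorithm:** "In the case of progressive or severe hypersensitivity, treat appropriately and withdraw the subject from the study".
- **Appendix 2, item 2:** those whose reaction is severe "will be evaluated according to the WHO Drug Toxicity criteria and there may be a discontinuation of treatment according to the protocol".

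Section 6.3.3 also has a separate bullet based on WHO grade: permanent discontinuation after at least two Grade 3 toxicities, or at least one Grade 4, that the investigator associates with the drug.

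Two scales feed these rules. Appendix 3 sorts clinical signs into Early, Moderate, Progressive and Severe, and places bronchospasm (glossed as wheezing) under Severe with no qualifier. The allergy row of Appendix 5 places "urticaria, drug fever 38°C (100.4°F), mild bronchospasm" at Grade 2, bronchospasm that needs parenteral medication at Grade 3, and anaphylaxis at Grade 4. The tolerability table in Appendix 2 uses the WHO grades: Grade 1 or 2 signs that respond to a slower infusion or to treatment count as poor tolerability.

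**The concern.** A site that follows the cross-reference in Section 6.3.3 meets two rules for the same reaction. Appendix 3 leaves no discretion. Appendix 2 inserts a grading step and makes discontinuation a possibility. Because the grading step uses a scale that ranks bronchospasm differently, the choice of appendix can change the outcome.

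What is at stake is whether a child who has had a reaction classed as severe is infused again. The number of subjects withdrawn for hypersensitivity, a safety result in its own right, also rests on which text each site applied. Appendix 4 foresees about 10 subjects at 5 to 10 sites, an average of 10/10 = 1 to 10/5 = 2 children per site, so a common reading is unlikely to form through experience. Section 6.3.4 does not replace withdrawn subjects, and each is 1/10 = 10% of the trial.

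**Working it through.** No figure in the protocol is in question, so the check sets the passages side by side.

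**Step 1. The rule for severe hypersensitivity.** The synopsis, Section 6.3.3 and Appendix 3 require withdrawal. Appendix 2 item 2 requires a WHO evaluation, after which discontinuation is possible. Three texts are mandatory and one is conditional.

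**Step 2. What the closing words of item 2 point to.** Item 2 refers back to the protocol without saying which rule it means. Section 6.3.3 offers two candidates.

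- *The hypersensitivity bullet.* Withdrawal then always follows, the WHO evaluation decides nothing, and *may* is the wrong verb.
- *The WHO-grade bullet.* Discontinuation then needs at least two Grade 3 toxicities or at least one Grade 4.

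The text does not choose. The mention of WHO criteria leans towards the second; the subject matter leans towards the first.

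**Step 3. Bronchospasm under each route.**

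| Reaction | Appendix 3 class and result | Appendix 5 grade | Result by the WHO-grade bullet alone | Appendix 2 tolerability class |
|---|---|---|---|---|
| Mild bronchospasm that responds to a slower rate or to treatment | Severe: withdraw | 2 | Not triggered (no Grade 3, no Grade 4) | Poor tolerability; no withdrawal in the visible text |
| One bronchospasm needing parenteral medication | Severe: withdraw | 3 | Not triggered (1 Grade 3, below 2; no Grade 4) | Not among the Grade 1 or 2 signs that define poor tolerability |
| Anaphylaxis | Not listed by that name; its Severe signs lead to withdrawal | 4 | Triggered (1 Grade 4) if judged drug-related | Not among the Grade 1 or 2 signs that define poor tolerability |

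**Step 4. Reading the table.** In the first row the two scales give different classes for the same sign, and only one class leads to withdrawal. In the second row the outcome differs only if item 2 is read through the WHO-grade bullet; the hypersensitivity bullet still requires withdrawal. In the third row a drug-related reaction ends treatment by either route. The disagreement therefore lies at Grades 2 and 3, not at the top of the scale.

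**The case against.** The strongest reply is that the protocol already says which text governs. Appendix 3 presents itself as the algorithm for hypersensitivity, and three places agree on withdrawal. Appendix 2 concerns infusion rate; its item 2 stands in a list introduced as assumptions and refers back to the protocol. The bullets in Section 6.3.3 are each sufficient alone, so a single Grade 3 bronchospasm leads to withdrawal through the hypersensitivity bullet even though the grade bullet is not met. The Appendix 2 figure, which is not shown, may also say what follows poor tolerability.

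Much of this stands. It makes withdrawal the more natural reading for a severe reaction and reduces the Grade 3 case to a consequence of one reading of item 2. It does not remove the conflict in words, because Section 6.3.3 sends the reader to Appendix 2 for this very decision. Nor does it explain why mild bronchospasm is Severe on one scale and Grade 2 on the other.

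Several stronger readings are tempting, and the documents do not support them.

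- *That Appendix 2 also softens the rule for progressive reactions.* Item 2 names only severe ones.
- *That hypotension is a further contradiction.* Appendix 3 lists mild hypotension under Moderate, and Appendix 5 grades hypotension by the treatment it needs, so Grade 2 does not automatically equal Severe.
- *That rash is a further contradiction.* Appendix 3 puts urticaria under Moderate and only "Erythematous or massive urticarial rash" under Progressive. Premedication is for subjects with "early clinical signs of hypersensitivity or rash/urticaria that responds promptly to oral antihistamine administration", and its stated aim is to prevent progression. These entries can be read together.

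**Conclusion.** The point holds in a limited form. Appendix 2 item 2 conflicts with the synopsis, Section 6.3.3 and Appendix 3 on whether severe hypersensitivity leads to withdrawal, and bronchospasm is classed inconsistently between Appendices 3 and 5. This rests on the visible text; the sponsor should check the Appendix 2 figure against it. It takes no view on which rule is clinically right.

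The size cannot be expressed as a probability. A reader might project the pivotal study's 2 hypersensitivity discontinuations among 32 patients (6.25%) onto 10 children. That would estimate the chance of any such discontinuation, not of a reaction on which the passages disagree, and it would carry a rate from a 38-week study into a 52-week one.

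A reader might also infer that the set of children with Month 12 data hangs on the passage applied. Section 6.3.3 asks for attempted follow-up for the full study, or at least 30 days, after discontinuation, and for every effort to complete the Visit 28 procedures, so that does not follow.

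The passages still need correcting, because they bear on whether a child is re-exposed after a severe reaction.

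**What to change.** Amend the protocol so that a severe hypersensitivity reaction leads to one stated outcome wherever it is described:

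1. Reconcile Appendix 2 item 2 and the Appendix 2 tolerability table with Section 6.3.3 and Appendix 3, and confirm that the Appendix 2 algorithm figure agrees.
2. State which scale, the Appendix 3 sign classes or the WHO grades, governs withdrawal for hypersensitivity, and how the WHO-grade bullet in Section 6.3.3 relates to the hypersensitivity bullet.
3. Make the bronchospasm entries in Appendix 3, Appendix 5 and the tolerability table consistent for the purpose of that decision.

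The medical lead chooses the outcome for each entry. The cost is amendment wording; the design, sample size and assessments are unchanged.
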